### Effectiveness

Prior to formal statistical analyses that evaluate effectiveness outcomes, we will first summarize demographic and baseline characteristics across study treatment arms to gauge comparability of Pre-I participants who consented to REDCap PRO surveys, as well as patients randomized to UC or EC during post-I. For each cancer treatment stratum (curative, non-curative, survivorship), we will calculate summary statistics for variables including gender, language preference, age, race/ethnicity, cancer diagnosis, and cancer stage. Means and standard deviations or medians and interquartile ranges will be used for continuous variables. Tables of frequencies and counts will be used for categorical variables. Summaries will be calculated both within each cluster and collapsed across all clusters. We expect baseline characteristics to be comparable across Pre-I, UC and EC groups since all eligible patients will be approached for participation in the study in both the pre- and post-implementation phases, and since patients will be randomized 1:1 to UC or EC. It is expected that stratified randomization in the patient-randomized trial will ensure balance of the treatment arms across cluster, cancer continuum, gender, and language preference.

For final reporting of effectiveness results, the following clinical and demographic variables will be included in descriptive summaries: NMHC cluster, cancer care continuum strata (curative, non-curative, survivorship), preferred language, participant's gender, age at enrollment and self-reported race/ethnicity. Primary and secondary outcomes will also be tabulated and summarized for manuscripts that are prepared to address these outcomes. Other clinical and demographic variables may also be included for description of the NU IMPACT study population.

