#### INCLUSION CRITERIA:

##### 1. Curative Intent Group:

- ≥ 18 years of age;
- medical chart confirmed diagnosis of a solid or hematological malignancy within the last 10 years;
- had an appointment at a participating site with a participating oncologist in the last year;
- willingness to be randomized (post-implementation only);
- have initiated primary treatment with curative intent within the past 3 months (i.e., as patients receive surgery, standard- or high-dose chemotherapy, biological therapy, and/or radiotherapy);

- provider confirmed planned treatment and follow-up within the Northwestern Medicine hospital and clinics;
  - provider confirmed planned treatment and follow-up within the Northwestern Medicine hospital and clinics; and
  - able to read English or Spanish.
2. Non-Curative/Palliative Intent Group:
- ≥ 18 years of age;
  - medical chart confirmed diagnosis of advanced or metastatic solid or hematological malignancy within the last 10 years;
  - had an appointment at a participating site with a participating oncologist in the last year
  - provider confirmed planned treatment and follow-up within the Northwestern Medicine hospital and clinics;
  - willingness to be randomized (post-implementation only);
  - undergoing cancer treatment with non-curative/palliative intent (e.g., patients with advanced or metastatic disease who receive chemotherapy, biological therapy, and/or radiotherapy to control or slow advance of their disease);
  - provider confirmed planned treatment and follow-up within the Northwestern Medicine hospital and clinics; and
  - able to read English or Spanish.
3. Cancer Survivorship Group:
- ≥ 18 years of age;
  - medical chart confirmed diagnosis of solid or hematological malignancy within the past 10 years;
  - had an appointment at a participating site with a participating oncologist in the last year;
  - provider confirmed planned treatment and follow-up within the Northwestern Medicine hospital and clinics;
  - willingness to be randomized (post-implementation only);
  - completed active cancer treatment with curative intent, including those who may be receiving maintenance or prophylactic cancer treatment;
  - provider confirmed planned cancer follow-up care (with or without treatment) within the Northwestern Medicine hospital and clinics; and
  - able to read English or Spanish.

### Aim 3

- *Clinician Focus Groups*

- Clinical or operational leader in an NM clinic participating in cPRO implementation

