#### Consented Patients:

Data from REDCap will be linked to utilization/clinical data from the EDW through an ‘honest broker’ (NM EDW analyst) who will link study data from REDCap to data from the EDW. The data will be considered a limited dataset because zip code will be included for analyses related to social determinants of health. The EDW analyst will automate exports stripped of sensitive protected health information (e.g., encounters related to substance abuse or providers related to a psychiatric specialty) and any identifiable information, except zip code. Data exports will be generated quarterly and will be saved to a shared folder on Northwestern’s secure FSMresfiles system with access restricted to NU IMPACT study personnel. Once EDW data has been extracted and shared with study team, there will be no efforts to re-identify data. Previous studies led by Drs. [name] and [name] have demonstrated their ability to pull reliable and comprehensive health service usage data from NM’s EHRs across all geographic regions. They have developed a query that includes date (for this project dates will be converted to days from date of consent) and type of health care contacts, clinic/department, and provider. Data from all eligible records can be pulled from EHRs and NM Tumor Registry by the EDW and delivered to study statisticians as a limited data set. Working with oncology clinicians, the research team developed a coding schema to summarize the available health usage data. Major categories include in-person (medical visit) and telephone contacts and MyChart communications and usage; sub-categories include relevant departments (Medical, Surgical, Radiation and Supportive Oncology; Palliative and Emergency Care; Integrative Medicine; Other specialty, such as, referral encounters related to rehabilitation (PT, OT, Speech); Internal Medicine; Lab services). In-person contacts have an additional classification for inpatient or outpatient encounters. Usage will be summarized as the number of encounters within and across categories within set timeframes. Additionally, confounding factors will be extracted: sex, age, zip code, cancer type and stage, treatment type, time since diagnosis, time since last treatment, comorbidities, race/ethnicity, and language preference.

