## **10.0 Recruitment Methods:**

### Aim 2

Participants will be drawn from the pool of NM cancer patients across the four regions. Specifically, patients of a clinician who has agreed to have his or her patients contacted and meet the eligibility criteria as stated above.

Each night, an EDW pull will flag patients based on the eligibility algorithm) based on clinical unit randomized rollout. Each day, this list of patients will automatically populate into a REDCap project. Logic will be included to remove duplicates. An email will be sent to the newly populated patients informing them of the project (see Survey Email Templates under the Recruitment Materials section of this modification). Each patient will receive a customized link. Patients who are interested in participating can click on that link, which will take them to REDCap to complete the consent form and study measures. We may also reach out by phone.

Patients who consent and complete the baseline survey will be sent additional customized links to complete the survey monthly after baseline for one year. For these surveys, patients will receive a reminder email or text message every 3 days for up to 4 reminders over 14 days, and we may also reach out by phone. These reminders will only be sent if the participant has not started their survey.

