To enhance representation of Latino/a English and Spanish-speaking participants in our post-implementation phase, we plan to diversify our recruitment strategy by including some targeted in-person recruitment in the clinics. In partnership with our clinical lead and co-investigator [name] (who will be able to facilitate EPIC access to NM schedules for research staff with Level 3 access), we plan to identify eligible Latino/a English and Spanish-speaking patients from the standardized EDW pull that flags patients based on the eligibility algorithm (described above) and then approach patients in the clinic before their next scheduled appointment. The research team has requested and received EDW exception approval to utilize EPIC access for recruitment purposes and these details are in compliant with that request. Research staff will work with clinic leads to determine optimal recruitment locations, but we anticipate that this will likely happen in the waiting room or in a treatment room. Participants will be approached and asked if they would like to hear more about a research opportunity using the IRB approved text that is in the recruitment e-mails. If a patient is interested in participating, the coordinator will manually enroll and e-consent the patient using the standard approved platform in REDCap with an approved, password protected study lap-top computer. The participant will then receive information via e-mail on their randomization status and how to start completing forms. Patients who decline participation will be documented in a separate password protected tracking sheet.

### Aim 3

- *Clinician Focus Groups*

- Clinicians and administrators will be recruited using a purposeful sampling strategy to recruit key stakeholders cross-regionally. Stakeholders who have been exposed to clinical cPRO procedures for a minimum of one year will be considered an eligible and recruited by email to assess potential interest in participating in a focus group. Stakeholders will have the option to decline participation. Focus group meeting coordination will be arranged around interested participant's schedules.

- *Patient-facing Interviews*

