Recognizing the possibility of contamination effects for the treatment arms during the post-I period, we will augment the primary analyses to include longitudinal PRO data from the Pre-I period. Linear mixed models will be used as described for the primary analyses but extending the primary predictor of interest to a multicategory variable (Post-I EC, Post-I UC, Pre-I). Adjustments for cluster, cancer continuum, gender, language preference, baseline PRO value and time of enrollment, and the individual-level random effects, will be included as described above. The Post-I UC cohort will be treated as the referent group to facilitate formal primary comparison with outcomes for the Post-I EC group, and to gauge comparability of outcomes for Post-I UC and Pre-I patients. This approach will also allow for a contrast test between Post-I EC and Pre-I. If longitudinal PROs for Post-I UC and Pre-I are not significantly different, and if the effectiveness estimate for Post-I EC v. Pre-I is similar to the primary Post-I EC v. Post-I UC comparison, this will suggest lack of contamination. If longitudinal PRO differences for Post-I UC v. Pre-I are significantly different and/or the effectiveness estimate for Post-I EC v. Pre-I is different from the primary Post-I EC v. Post-I UC comparison, this may suggest some level of treatment arm contamination during the Post-I phase. This latter scenario may also be indicative of system-level implementation effects and will need to be interpreted in the context of implementation analysis findings.

Multiple imputation using chained equations will be used for missing data under a range of scenarios from missing at random to informative missingness. Sensitivity of parameter estimates to these assumptions will be evaluated.

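### Recruitment differs between the pre-I and post-I phases, but the SAP expects Pre-I to be comparable, leaves already-extracted confounders out of the Pre-I contrasts, and does not name selection as an explanation for a difference

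*Combined protocol and SAP*

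**What the plan says.** **Comparability.** SAP 7.2 (Descriptive Analyses, Effectiveness) expects Pre-I, UC and EC to be alike at baseline because "all eligible patients will be approached for participation in the study in both the pre- and post-implementation phases". It also cites the 1:1 randomisation as support.

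**Recruitment.** In Protocol 10.0 the general route starts from a nightly data-warehouse pull: "An email will be sent to the newly populated patients informing them of the project". Phone contact is also possible. For Latino/a English- and Spanish-speaking patients the protocol then adds that, "in our post-implementation phase, we plan to diversify our recruitment strategy by including some targeted in-person recruitment in the clinics". Protocol 3.0 lists "willingness to be randomized (post-implementation only") among the inclusion criteria of all three patient groups. SAP 2.0 makes patients who consented during pre-I ineligible for randomisation later. SAP 4.0 describes recruitment to the randomised trial as running through MyChart and does not mention the in-person route.

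**Adjustment.** For the three-group PRO model, SAP 9.1 says: "Adjustments for cluster, cancer continuum, gender, language preference, baseline PRO value and time of enrollment, and the individual-level random effects, will be included". Enrolment time enters as a categorical quarter. The utilisation model in SAP 9.2 has the same strata and enrolment time but lists no baseline value. Protocol 8.0 (Consented Patients) says that "confounding factors will be extracted: sex, age, zip code, cancer type and stage, treatment type, time since diagnosis", and goes on to name time since last treatment, comorbidities, race/ethnicity and language preference. Further adjustment for detected imbalances is planned only in SAP 9.3, for the exploratory hazard and odds ratios.

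**Interpretation.** SAP 9.1 treats a UC v. Pre-I difference, or an EC v. Pre-I estimate unlike the EC v. UC estimate, as a possible sign of contamination, and alternatively of system-level implementation effects.

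**The concern.** Randomisation makes EC and UC comparable. Nothing in the design does so for Pre-I. Three things that can affect who enrols change between phases: the mode of contact, the consent condition and the source pool. Being approached in both phases does not mean that the same kinds of patients consent.

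The adjustment covers part of this. Language preference picks up Spanish-preferring recruits, but Protocol 4.0 expects only about 40% of Hispanic participants to be Spanish monolingual or Spanish-preferring, and the in-person effort also targets English speakers. Age, race/ethnicity, diagnosis and stage are tabulated under SAP 7.2 but do not enter the PRO models.

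At stake is the reading of a comparison that SAP 3.0 regards as critical for detecting contamination. A recruitment difference would be assigned to one of the two explanations offered. Selection in the opposite direction could hide contamination that did occur. The second trigger in SAP 9.1, a dissimilar EC v. Pre-I estimate, requires no significance test, so bias alone could set it off.

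**Working it through.** **1. The SAP's own figure (SAP 6.0).** Inputs: compound symmetry with correlation 0.5, difference 0.3 SD, alpha 0.01 (taken as two-sided), power 90%, 12 follow-up visits.
- Variance of a 12-visit mean = (1 + 11 × 0.5)/12 = 0.5417.
- n per arm = 2 × (2.576 + 1.282)² × 0.5417/0.3² = 179.1, so 180 per arm and 360 in total. 360/(1 − 0.64) = 1000. Both figures reproduce and are not in dispute. The same variance structure is used below.

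**2. Bias from a recruitment difference.** The documents give neither the share of in-person recruits nor how far they differ. Assume that they form 10–25% of post-I and differ stably by 0.3–0.5 SD.
- Raw offset = share × difference: 0.10 × 0.3 = 0.03 SD up to 0.25 × 0.5 = 0.125 SD.
- With correlation 0.5 the slope on baseline is 0.5, so baseline adjustment leaves half: 0.015 to 0.0625 SD.
- An offset that emerges only after baseline is not reduced in this way.
- A constant post-I offset falls entirely on the group term, so cluster and quarter do not reduce it.

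**3. Standard error without cluster and quarter.** Assume 500 per group (the SAP gives no Pre-I target; 500 is half of its randomised target of about 1,000) and no dropout.
- Residual variance = 0.5417 − 0.5² = 0.2917.
- SE = √(2 × 0.2917/500) = 0.034 SD.
- Two-sided 5% rejection at 0.015, 0.03 and 0.0625 SD: about 7%, 14% and 45%.

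**4. Standard error with the SAP's covariates.** In SAP Figure 2 each cluster recruits Pre-I patients for two quarters and randomised patients for the next two, so phase is partly collinear with cluster and quarter. Take seven equal clusters, cluster c recruiting Pre-I in quarters c and c+1 and UC and EC in quarters c+2 and c+3, with 500/14 patients per cell. Fit three groups, seven clusters and ten quarters, with residual variance 0.2917.
- SE for Pre-I v. UC = 0.067 SD, about double.

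| Bias (SD) | Bias/SE | P(significant), no dropout | P(significant), 36% retained |
|---|---|---|---|
| 0.015 | 0.22 | 5.6% | 5.2% |
| 0.03 | 0.45 | 7.3% | 5.8% |
| 0.0625 | 0.93 | 15% | 8.6% |

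The last column uses SE = 0.067/√0.36 = 0.112, from the 64% dropout that SAP 6.0 allows for.

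**5. A narrower input.** Protocol 4.0 expects 13% Hispanic participants. Those not Spanish-preferring would be 13% × 60% = 7.8%. At 0.3–0.5 SD the offset is 0.023–0.039 SD raw and about 0.012–0.020 SD after baseline adjustment, a false-signal rate near 5–6%. This is not a ceiling, since the in-person effort aims to raise that share.

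**The case against.** The strongest reply is that the SAP has done more than it is given credit for. A reader might infer that the Pre-I contrasts adjust for the randomisation strata alone. They do not: the PRO model also includes baseline PRO and enrolment quarter, and the working shows that both matter.

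A reader might also infer that the protocol contradicts SAP 7.2. It does not, literally. In-person candidates come from the same data-warehouse pull as e-mail candidates, so all eligible patients may still be approached in both phases. SAP 7.2 phrases comparability as an expectation and tabulates age, race/ethnicity, diagnosis and stage, so a visible shift would be seen before the contrasts are read. SAP 9.1 is hedged and has no automatic rule for declaring contamination.

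The false-signal rates of up to 45% in step 3 are a further tempting reading. They leave out cluster and quarter, which the SAP's model contains, and should not be used.

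Finally, no proposed covariate measures willingness to be randomised or mode of contact. That is correct, and it limits what the remedy can do.

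All of this reduces the size of the point but does not remove it. Tabulating an imbalance does not adjust for it, the interpretation text still omits selection, and SAP 9.3 already accepts further adjustment in principle for other outcomes.

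**Conclusion.** The point holds as a cheap improvement to a supporting, non-randomised analysis. Recruitment differs by phase, the comparability statement extends to a group that randomisation does not cover, available confounders are left out, and selection is missing from the listed explanations.

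The size is probably modest: a bias of 0.015–0.0625 SD, against the 0.3 SD effect used for planning, and a false-signal rate of about 6–15% instead of 5%. This rests on assumed shares and differences, 500 per group, equal clusters, even recruitment across quarters and no dropout. Dropout lowers the rates. Larger groups would raise them (Protocol 4.0 gives 6,336 for the pre-implementation cohort), but the bias itself does not depend on group size. Selection through willingness to be randomised is not in these figures and cannot be sized from the documents.

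A reader might infer that the primary effectiveness result is at risk. It is not: that estimate compares EC with UC, both randomised within post-I.

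**What to change.** - **SAP 9.1 and 9.2, Pre-I contrasts:** add a sensitivity model that also adjusts for the confounders extracted under Protocol 8.0 (age, race/ethnicity, cancer type and stage, treatment type, time since diagnosis, time since last treatment, comorbidities). This extends the approach of SAP 9.3.
- **Same contrasts:** repeat them without in-person enrolees, where the enrolment route can be identified. Protocol 10.0 describes manual enrolment by the coordinator but states no route flag, so this should be confirmed.
- **SAP 9.1, interpretation:** name differences in who was recruited as a third explanation for a UC v. Pre-I difference, and note that selection could also mask contamination.
- **SAP 7.2:** limit the statement of comparability by design to UC v. EC.
- Leave the randomised EC v. UC model unchanged.

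The cost is one extra model, some SAP wording and some loss of precision in the Pre-I contrasts. SAP 1.0 says that changes to the SAP need no protocol amendment. Covariate adjustment will not remove selection through willingness to be randomised, and the report should say so.

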## 8.0 STATISTICAL ANALYSES - IMPLEMENTATION

### 8.1 Primary Outcome - Implementation

#### Reach (proportion of patients)

Reach will be measured by the proportion of patients completing one or more ( $\geq 1$ ) cPRO assessments among those eligible for cPRO. This analysis will be a clinic-level analysis analyzed under a cross-sectional design and will only include clinics in the 6 clusters that were randomized. We will calculate reach using 1-month sampling periods within each clinic (as less than 100 individuals in a clinic would be too small for a per-month analysis, our back up will be a 2-month sampling period rather than a 1-month sampling period). The outcome variable will be defined as the proportion of participants who complete a cPRO assessment among those who are eligible within the clinic and the 1-month period. Thus, each month and clinic will have a single data point expressed as a proportion of eligible individuals reached. There are approximately 30 clinics (median of 5 clinics per cluster) and 42 monthly reach proportions will be calculated for each clinic; thus we anticipate 1260 data points for the primary outcome variable. We will use the nlme package in R to perform generalized least squares linear regression modeling with an exposure indicator variable for post-I v. pre-I [referent] entry into the study as the primary predictor of interest. An autoregressive structure will be specified for the correlation structure among the linear model residuals resulting from the repeated measurements of reach within clinic; a lag 1 model will be specified, but model fit under this and other correlation structure specifications will be evaluated according to AIC and BIC. In the generalized least squares setting, the within-clinic repeated measures observation structure is used to define the structure of the covariance matrix. The degrees of freedom is thus the number of calculated proportions calculated for all 1-month intervals and all clinics, less the number of model parameters, including those specified in the covariance matrix. We will perform analyses using an identity link for the outcome variable to estimate risk differences on the raw proportions. In addition, we will log-transform the outcomes to estimate relative risk ratios. We will use clinic-level covariate adjustment for: 1) cluster; 2) time (categorical variable for quarter); 3) number of 1.0 FTE equivalent oncologists per clinic; 4) number of unique patients per clinic; and 5) type of cancer care clinic (e.g., medical oncology, surgical oncology). In sensitivity analyses, we will use weights in the generalized least squares model based on the number of unique eligible patients per clinic. Restricted maximum likelihood (REML) will be used for model parameter estimation as it produces unbiased estimates of the variance and covariance parameters. The primary predictor of interest will be post-I v. pre-I entry into the study, i.e. whether the individual became eligible for cPRO during the pre-I or post-I phase at their site. This clinic-level analysis was chosen as we hypothesize that the impact of the implementation strategy will vary by clinic due to clinic size (clinicians and patients). We will also test for cluster\*treatment and time\*treatment effects to test for a lagged/delayed effect of the exposure, and clinic effects within clusters, in the overall model. Rather than including an a priori transition period, we will conduct a sensitivity analysis around the crossover point in two 1-month increments.

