### 3.0 STUDY DESIGN

#### Implementation Study

A schematic of the study design that illustrates the test of the implementation strategy package is depicted in Figure 1. All clusters will begin with a 6-month pre-I period of data collection. We will use a stepped-wedge trial design comprising seven total clusters. Clusters are the unit of randomization. We will use non-random assignment of the first cluster in the sequence, which was based on readiness to start on our proposed time table, followed by simple randomization of the remaining six clusters to the time of transition from pre-I to post-I. The seven clusters contain 32 clinics (1-9 clinics per cluster). The clinics comprising each of the clusters largely follow naturally occurring administrative structures within the health system (e.g., they share operational leadership). Possible times of transition from pre-I to post-I will follow a quarterly schedule. This will allow within- and between-site evaluation of system-level changes due to prospective introduction of implementation strategies in the observational group of patients completing cPRO assessments and being triaged and referred for relevant clinical services based on their assessment results, under UC. Importantly, the majority of implementation strategies within the package begin immediately prior to or at the point of each cluster's transition from pre-I to post-I.

|           | Year 3 |       |        |        | Year 4 |        |        |        | Year 5 |        |        |        | Year 6 |        |    |    |
|-----------|--------|-------|--------|--------|--------|--------|--------|--------|--------|--------|--------|--------|--------|--------|----|----|
|           | Q1     | Q2    | Q3     | Q4     | Q1     | Q2     | Q3     | Q4     | Q1     | Q2     | Q3     | Q4     | Q1     | Q2     | Q3 | Q4 |
| Cluster 1 | pre-I  | pre-I | post-I | post-I | post-I | post-I | post-I | post-I | post-I | post-I | post-I | post-I | post-I | post-I |    |    |
| Cluster 2 | pre-I  | pre-I | pre-I  | post-I | post-I | post-I | post-I | post-I | post-I | post-I | post-I | post-I | post-I | post-I |    |    |
| Cluster 3 | pre-I  | pre-I | pre-I  | pre-I  | post-I | post-I | post-I | post-I | post-I | post-I | post-I | post-I | post-I | post-I |    |    |
| Cluster 4 | pre-I  | pre-I | pre-I  | pre-I  | pre-I  | post-I | post-I | post-I | post-I | post-I | post-I | post-I | post-I | post-I |    |    |

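### The primary stepped-wedge test allows correlation within clinic only, so it is anti-conservative if the clinics of a randomised cluster move together over time

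*Combined protocol and SAP*

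**What the plan says.** SAP 3.0 (Implementation Study) states: "Clusters are the unit of randomization". The first cluster is placed without randomisation, "followed by simple randomization of the remaining six clusters to the time of transition from pre-I to post-I". Figure 1 shows one cluster crossing at each quarterly step. The clinics forming a cluster "largely follow naturally occurring administrative structures within the health system (e.g., they share operational leadership".

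SAP 8.1 says the primary reach analysis "will only include clinics in the 6 clusters that were randomized". On the amount of data it says: "There are approximately 30 clinics (median of 5 clinics per cluster) and 42 monthly reach proportions will be calculated for each clinic". From this it expects 1,260 outcome values in all. The model is generalised least squares fitted by REML, with an AR(1) structure for the repeated values from the same clinic. Other correlation structures are to be compared by AIC and BIC. Covariates are cluster, calendar quarter, oncologist FTE, patient volume and clinic type. On the reference distribution it says: "The degrees of freedom is thus the number of calculated proportions calculated for all 1-month intervals and all clinics", minus the mean and covariance parameters.

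For this outcome the SAP plans no random cluster or cluster-by-period term, no cluster-robust variance, no small-sample correction and no randomisation test. SAP 8.2 reuses the framework for the other reach outcomes and for provider adoption. The only cluster-level analysis is a fallback for provider adoption when a clinic has fewer than 20 clinicians.

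Protocol 4.0 describes the roll-out as randomised inside each region. SAP 3.0 mentions no such restriction.

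**The concern.** All clinics in a cluster switch on the same date, so the exposure varies only between clusters and over time. The information about the effect comes from six cluster trajectories. The planned covariance treats two clinics of the same cluster as independent once the covariates are fitted. The fixed cluster term takes out a constant level difference, and the quarter term takes out trends common to the whole system. Neither takes out a cluster's own drift, for example after a change of shared management or staffing. With one cluster per step there is no second cluster at the same step to reveal how large that drift is.

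If such drift exists, the model standard error understates the variability of the estimate, and the test of the primary implementation hypothesis rejects too often. The same would apply to the secondary outcomes in 8.2.

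**Working it through.** **1. The plan's own figure.** Figure 1 has 14 quarters of data: 14 x 3 = 42 months. 30 clinics x 42 = 1,260 points, as stated.

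**2. Degrees of freedom under the stated rule.** Parameters: intercept 1, exposure 1, cluster 5, quarter 13, FTE 1, volume 1, clinic type 1 to 4 (2 to 5 types assumed), AR(1) correlation and variance 2. The total is 25 to 28. Then 1,260 - 28 = 1,232 and 1,260 - 25 = 1,235. The two-sided 5% critical value is 1.96. (The SAP states no alpha for this test; 5% is assumed.) With the fallback of 2-month periods there are 630 points and 602 to 605 df, and the critical value is again 1.96.

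**3. Hand check of the standard error.** Let s be the share of time-varying residual variance common to a cluster's clinics. The documents give no value for s. With 5 clinics per cluster, the time-varying variance of a cluster mean is (1 - s)/5 + s. The model assumes 1/5. The ratio is 1 + 4s, so the true SD exceeds the model SE by a factor of √(1 + 4s):
- s = 0.10: √1.4 = 1.18; rejection P(|Z| > 1.96/1.18) ≈ 10%
- s = 0.25: √2 = 1.41; ≈ 17%
- s = 0.50: √3 = 1.73; ≈ 26%

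**4. Simulation of the stated model under no effect.** Six clusters x 5 clinics x 42 months, with the six randomised transition times of Figure 1. Outcome = √(1 - s) x clinic AR(1) + √s x cluster AR(1). The fit was REML GLS with within-clinic AR(1), fixed cluster and fixed quarter; the other clinic covariates were left out. Autocorrelation was 0.6, with 2,000 runs per row:

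| s | Rejects at nominal 5% | 95% CI coverage | True SD / model SE | Rejects with 5 df |
|---|---|---|---|---|
| 0 | 4.7% | 95% | 1.0 | 1.3% |
| 0.10 | 10.6% | 89% | 1.2 | 3.2% |
| 0.25 | 17.3% | 83% | 1.4 | 7.0% |
| 0.50 | 27.5% | 73% | 1.8 | 16.0% |

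**5. Range over settings.** One set used autocorrelation 0.3, 0.6 and 0.8, with and without a clinic intercept variance equal to the residual variance (600 runs each). A second set used 0.5 or 0.8, equal and unequal clusters, with and without clinic intercepts (300 runs each).

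| s | First set | Second set | Combined |
|---|---|---|---|
| 0 | 3.5-5.8% | 2-7% | 2-7% |
| 0.10 | 4-11% | 8-12% | 4-12% |
| 0.25 | 10-17% | 13-20% | 10-20% |
| 0.50 | 19-29% | 20-31% | 19-31% |

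**6. Changing the df alone.** With 5 df (6 clusters - 1, as an illustration) the critical value is 2.57, and 2.57/1.96 = 1.31, so intervals are 31% wider. The last column of the table in step 4 shows that this is too strict at s = 0 and not strict enough at s = 0.25 and 0.50. The standard error itself is wrong.

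**7. Randomisation test.** Under simple randomisation there are 6! = 720 orders. The smallest p is 1/720 = 0.0014, or 2/720 = 0.0028 counting both tails. A permutation test over all 720 orders, using the cluster- and quarter-adjusted difference on cluster-quarter means, rejected 4.4% to 5.9% at every s in step 4 (autocorrelation 0.6, clinic intercepts included, 2,000 runs each).

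**8. If roll-out was randomised within region.** Protocol 5.0 names four regions. How the six clusters fall into them is not given. If they span all four, at most 3! x 1 x 1 x 1 = 6 orders exist, and the smallest p is 1/6 = 0.17. If they span three (assumed), there are 2! x 2! x 2! = 8 to 4! = 24 orders, and the smallest p is 0.125 to 0.042 before doubling for two tails.

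**The case against.** The strongest reply is that nothing in the documents shows clinics in a cluster drifting together. With no sharing the planned test is close to nominal. With weak autocorrelation (0.3) and large stable clinic differences it rejected only 4.2% at a 10% share. All of that stands, and it makes the size of the problem conditional. A reader might infer that the reported p-value and interval are certain to be too optimistic. The documents do not support that, because they give no value for the sharing. They do give a reason to expect some, namely shared operational leadership.

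Other features of 8.1 do not repair the gap. The AIC/BIC comparison concerns correlation among repeated values within a clinic. The interaction and clinic-effect tests, the weighting and the crossover sensitivity analyses add no between-clinic covariance to the primary test.

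Three further stronger readings should be set aside:
- **That the large df count is the fault.** At zero sharing it causes no inflation, and at high sharing 5 df does not remove it. The variance model is the main fault.
- **That a local campaign or staffing change would be read as an effect.** With randomised crossover times it mainly adds unmodelled variance. It imitates an effect only when it coincides with the crossover.
- **That the log scale undermines the primary result.** The SAP says "we will log-transform the outcomes to estimate relative risk ratios", and a month with no completers would be undefined there. But this is an additional analysis, no completion rates are given to show that such months will occur, and the raw-proportion analysis is unaffected.

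It is also fair to object that a randomisation test is no safe replacement as the sole primary test. If allocation was within region, it may be unable to reach 5%.

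**Conclusion.** The point holds in conditional form and should be settled before analysis. As written, the primary implementation test has no protection against cluster-specific change over time, although the cluster is the randomised unit and there are only six. Its true size at nominal 5% is about 2-7% with no sharing, 4-12% at a 10% share, 10-20% at 25% and 19-31% at 50%. In the main simulation, 95% interval coverage fell to 89%, 83% and 73% at those three shares.

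These figures assume the shares listed, AR(1) errors and a two-sided 5% level, and the simulations in steps 4 and 5 use autocorrelation of 0.3 to 0.8. The sharing is an assumption throughout. The missing between-clinic covariance, the df rule and the six randomised clusters are in the text. The patient-randomised comparison of enhanced and usual care in SAP 9.1 is not affected.

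**What to change.** 1. **Reconcile the allocation first.** SAP 3.0 and protocol 4.0 must state the same scheme, and the SAP should list the allocations that were possible.
2. **Change the model in 8.1, and in 8.2 where it is reused.** Replace the within-clinic-only covariance with random cluster-by-quarter effects in addition to within-clinic serial correlation. Replace the df sentence with a small-sample, cluster-based df correction. Both changes are needed.
3. **Report a randomisation test** over the allocations actually possible, with the regression estimate as the statistic.
4. **State in advance which analysis is primary.** If allocation was within region and there are too few orders to reach p < 0.05, the small-sample-corrected mixed model should be primary and the randomisation test supportive.

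The cost is SAP wording and some programming. No new data are needed, and SAP 1.0 says SAP changes need no protocol amendment. Intervals will be wider and power lower. SAP 6.0 gives no power calculation for this outcome, so the loss cannot be quantified from the documents. The corrected mixed model was not itself simulated here, so its size with six clusters should be checked before it is adopted.
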